The purpose of this article is to present a clinical protocol (PHRC “STIM-SD”*)* implementing a multi-day tDCS regime in a large population of patients with SD (*n* = 60) specifically targeting the left ATL (with anodal stimulation) or the right ATL (with cathodal stimulation) to provide evidence for potential therapeutic effects and brain plasticity outlasting the duration of the treatment. This intervention builds on a previous pre-therapeutic double-blind, sham-controlled study by our team using a single tDCS session applied to the left and right ATL in patients with SD [45]. This approach allowed the comparison of left anodal (excitatory) to right cathodal (inhibitory) tDCS stimulation and showed that a single session of both left anodal and right cathodal tDCS resulted in transient but highly significant intra-semantic effects [45]. The goals of the present study include the evaluation of the potential therapeutic efficacy of periodical sessions of tDCS over the ATL during 10 days in language/semantic performance in patients with SD, the assessment of the time course of potential improvements, the exploration of potential effects on brain plasticity using functional connectivity measures (resting-state functional magnetic resonance imaging (fMRI)) and cortical metabolism (fluorodeoxyglucose positron emission tomography (FDG-PET)), the identification of the most efficient stimulation modality (left-anodal versus right-cathodal) and the identification of biomarkers such as ATL atrophy levels, which could be individually indicative of an efficient tDCS impact.

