**Fig. 2 Fig2:**
[figure not shown]
The three upper panels show, respectively, **a** coronal, **b** axial and **c** sagittal sections from magnetic resonance imaging (MRI) in a representative patient with semantic dementia (SD). The crosshair signals the location of the stimulation target in the left Anterior Temporal Lobe (ATL). **d** MRI-based frameless stereotactic navigation system device (Brainsight) employed for accurate targeting of the left ATL in SD patients. 3D brain curvilinear **e** cortical and **f** skin reconstructions from the MRI of a patient, provided by the neuronavigation system with a sphere indicating the left ATL target aimed by the stimulation

Stimulation is delivered using a wireless hybrid EEG/tDCS 8-channel neurostimulator (Starstim, NEuroelectrics, Barcelona, Spain). The active electrode is placed over the left ATL for left-anodal tDCS (between 10 and 20 EEG coordinates ~ FT7 and FT9), while the cathodal tDCS targets the right ATL (between ~ FT8 and FT10). In sham tDCS stimulation, the active electrode is placed over the same MNI coordinates as left-anodal tDCS. The return electrode is placed over the contralateral supra-orbital region with regards to the active electrode location (10–20 EEG coordinates AF8 for left anodal tDCS and AF7 for right cathodal tDCS). Additionally, six EEG scalp electrodes (NG Geltrode® Ag/AgCl, 1.0 cm^2^) provided by the same tDCS device, which allow for continuous monitoring of brain activity during the session, are placed in 10–20 EEG system locations F4, F3, C4, C3 and P4, P3.

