### Computational models of tDCS current magnitude and distribution

There is evidence that the thickness of the skull, the volume of the cerebrospinal fluid in the subdural space and the distance from the targeted region in the brain to the tDCS anode or cathode account for up to 50% of the spatial variation of the electric field strength [61–63]. Kim et al. [64] found that performance improvement in a working memory task correlated with the simulated current magnitude, suggesting that inconsistent behavioral outcomes of tDCS might be partly due to individual anatomical differences.

A computational approach of modeling should allow for defining if and how tDCS current magnitude and distribution in the heads of individuals can differ and how these differences will affect clinical outcomes. Individual computational models will be produced using the open-source tool ROAST [65] to simulate tDCS current magnitude and distribution using the anatomical 3D T1-weighted MRI images of each patient (Fig. 5). Then, correlation will be tested between model-estimated data for current magnitude values and clinical data, specifically the changes in scores in the SA task from baseline to post-stimulation. A region of interest (ROI) will be defined and the mean of the 5% highest electric field values in this region will be obtained for each patient. More specifically, we will define the left anterior/middle temporal lobe as our ROI, because this region is primarily damaged in SD and it is the region targeted during the stimulation. Finally, measures of thickness of the different tissue layers (skin, skull, cerebrospinal fluid volume, gray matter and white matter) and distances between the stimulation target (ATL) and the stimulating electrode will be obtained and regression models will be computed to identify specific features that most influence changes in current magnitudes. This will allow us to identify the characteristics that might influence patients’ responses to tDCS and help predict if an individual patient might benefit from tDCS treatment.

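### The electric-field analysis measures the left temporal lobe in every patient, although the right-cathodal arm is stimulated over the right one

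*Protocol article*

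**What the plan says.** The section on computational models (protocol article, Methods) plans an individual simulation of the current for each patient and a correlation between the simulated field and clinical change, "specifically the changes in scores in the SA task from baseline to post-stimulation". It names one region of interest: "we will define the left anterior/middle temporal lobe as our ROI, because this region is primarily damaged in SD". The second reason given is that "it is the region targeted during the stimulation". On scope it says that "the mean of the 5% highest electric field values in this region will be obtained for each patient". No right-sided region is named, and nothing limits the left-sided one to the left-anodal arm. The worked example in Fig. 5 shows the left-anodal montage only.

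Elsewhere the targets differ by arm. The Introduction describes the trial as "specifically targeting the left ATL (with anodal stimulation) or the right ATL (with cathodal stimulation". Under Stimulation administration, separate left and right target coordinates are labelled on each patient's images. The active electrode is over the left anterior temporal lobe for left-anodal tDCS, "while the cathodal tDCS targets the right ATL". The return electrode changes side as well: "10–20 EEG coordinates AF8 for left anodal tDCS and AF7 for right cathodal tDCS".

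The Data analyses section gives the purpose: to learn which anatomical features determine how much current arrives at the target, and whether that amount helps to predict response.

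**The concern.** The analysis is meant to relate response to the current delivered at the target. For left-anodal patients the left-lobe field is that quantity. For right-cathodal patients it is the field in the hemisphere opposite the active electrode, on the side of the return electrode. The stated rule and its stated justification therefore disagree with the plan's own description of one of the two active arms.

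Two planned analyses are touched. The correlation of field with SA change would use an off-target exposure in that arm. The regression of current magnitude on anatomy would also be affected. One of its listed predictors is the distance from target to stimulating electrode. In the right-cathodal arm that distance is right-sided, while the field it has to explain is left-sided. At stake is whether a weak or absent relation could be read as showing that delivered current does not matter, when in half of the treated patients current at the target was not measured.

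**Working it through.** **Side by side**

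| Arm | Active electrode over | Return electrode | Region used for field | Is it the target? |
|---|---|---|---|---|
| Left-anodal (20) | left anterior temporal lobe | AF8, right | left lobe | yes |
| Right-cathodal (20) | right anterior temporal lobe | AF7, left | left lobe | no |
| Sham (20) | same site as left-anodal | not given separately | left lobe | same side, but current is off during the session |

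Allocation comes from Study design, electrode positions from Stimulation administration, and the region from the computational models section.

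**Share affected.** 20 / (20 + 20) = 50% of actively treated patients.

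**Effect on the correlation.** The article gives no power or expected correlation for this analysis, so there is no figure to reproduce. What follows is an illustration on assumed values.

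Let ρ be the true correlation between field at the target and SA change, equal in both active arms. Let c be the correlation, within the right-cathodal arm, between left-lobe field and right-target field. Assume that left-lobe field in that arm relates to response only through c, and that the arms have equal size, means and standard deviations. The correlation seen in the 40 active patients is then the average of ρ (left-anodal) and ρc (right-cathodal):

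r = ρ(1 + c)/2

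Power by the Fisher z approximation, n = 40, two-sided 5%: Φ(atanh(r)·√37 − 1.96).

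For ρ = 0.4 with the target-side region: atanh(0.4) = 0.424; 0.424 × 6.083 = 2.577; 2.577 − 1.96 = 0.617; power 73%.

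| ρ | Target-side region: power | c = 0: r, power | c = 0.5: r, power | c = 0.75: r, power |
|---|---|---|---|---|
| 0.3 | 47% | 0.15, 15% | 0.23, 29% | 0.26, 37% |
| 0.4 | 73% | 0.20, 23% | 0.30, 47% | 0.35, 60% |
| 0.5 | 92% | 0.25, 34% | 0.38, 67% | 0.44, 81% |

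Under these assumptions nothing is lost only if c = 1.

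**If the arms are pooled without an arm term.** Suppose also that the left-lobe field is lower in the right-cathodal arm by s standard deviations, with the same mean response in both arms. The field's variance becomes 1 + s²/4, so r is divided by √(1 + s²/4). For ρ = 0.4 and c = 0.5, r falls from 0.30 to 0.27, 0.21 and 0.17 for s = 1, 2 and 3. If mean response differed between arms as well, the bias could go either way.

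**The case against.** The best defence is that the left lobe was also chosen because it is the region mainly damaged, which is true in every arm. Right-cathodal stimulation is meant to help by releasing the left language network, so the field in one common, disease-relevant region is a reasonable exploratory measure. This stands as a reason to keep the left-lobe value. It does not make the left lobe the target: under that rationale the current acts on the right and the left-sided benefit is indirect. The article itself asks about current at the target.

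A reader might go further in three ways that the article does not support.

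- **That the planned result is confounded by arm.** The text says only that a correlation will be tested. It does not say that arms are pooled or that arm is left out, and an article may leave this to the analysis plan. It reports no field values by arm either.
- **That 40 of 60 patients (67%) carry an irrelevant value once sham is counted.** The wording about each patient concerns obtaining the field value, not who enters the correlation. The sham electrode sits over the left site, so the side is not wrong there. How sham values are used is open, which is not an error.
- **That most of the usable information is lost.** The smallest correlations detectable with 80% power, tanh(2.802/√(n − 3)), are about 0.59 for n = 20 and 0.43 for n = 40. They describe how small the trial is for this question, not the loss from using the wrong side. At c = 0.5 to 0.75 the loss is partial.

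It is also fair that the target-to-electrode distance is worded without a side. The fault lies in the field value with which that distance would be paired.

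**Conclusion.** The point holds in a limited form. The article fixes one left-sided region for all patients and justifies it partly by a statement that is untrue for the right-cathodal arm. In 20 of 40 actively treated patients (50%) the exposure is not the field at the target. That count follows directly from the article. The power loss does not: it rests on assumed values of ρ and c. At ρ = 0.4 power falls from about 73% to somewhere between 23% (c = 0) and 60% (c = 0.75). Confounding by arm is a possibility only if the arms are pooled without an arm term, which the text does not state.

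The analysis is secondary. The primary SA comparison at 2 weeks and the sample size do not depend on it. The correction is worth making because it amends a stated rule and needs no new data.

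**What to change.** In the computational models section, define the primary region as the anterior/middle temporal lobe under the active electrode: left for left-anodal, right for right-cathodal. Relate SA change to that field in the actively treated patients, either by arm or in one model with an arm term. Use the same target-side field in the regression on tissue thickness and target-to-electrode distance. Keep the left-lobe field in all arms as a labelled secondary measure, justified by the site of damage alone, and remove the statement that it is the stimulated region in every patient. It would help to add a sentence on whether and how sham patients' simulated values are used.

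The cost is a revised sentence or two and one extra mask. The simulations are already planned for each patient, and the right-sided target is already labelled on each patient's images.

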**Fig. 5 Fig5:**
[figure not shown]
Example of a computational model produced with the open-source tool ROAST for the simulation of transcranial direct current stimulation (tDCS) current magnitude and distribution using a 3D T1-weighted image from a representative SD patient. **a** Illustration of the montage for the left-anodal stimulation. The round blue patch represents the cathode, placed over the right supra-orbital region [10–20 electroencephalography (EEG) coordinates AF8], and the red round patch represents the anode, placed over the left Anterior Temporal Lobe (ATL) (Montreal Neurological Institute (MNI) coordinates: x = − 52, y = 2, z = − 28). **b** Coronal slice view of the electric field with current flow direction represented by the black arrows. **c** Electric field distribution on the cortical surface - right hemisphere view, left hemisphere view, upper view and frontal view. The color-bar represents the magnitude of the electric field, in Volts per meter, in different regions of the brain (for panels **b** and **c**)

### Data management

Data are collected via the eCRF that was developed at the outset of the study. All clinical and language/semantic task information required by the protocol is entered into the eCRF. The data are collected as and when they are obtained, and any missing data are clearly coded. Every investigator participating in the protocol has access to the eCRF via a web-based password-protected data collection system. All data are collected in the same center, the Pitié-Salpêtrière Hospital. Investigators have been given instructions for using this tool prior to the beginning of the protocol. Regular monitoring by the promoter of the study (APHP. Assistace Publique-Hôpitaux de Paris) will ensure the accuracy and quality of all the data and detect and address any issues related to the implementation.

All data collected on participants are anonymized through a specific number attributed to the participant at inclusion and his/her respective last and first name initials. Data collected in this study include both quantitative (neuropsychological and language standard tests scores, study task scores) and qualitative data (clinical history, neurological information). A print-out, authenticated by the principal investigator of the protocol, will be requested at the end of the research by the promoter of the study and the investigator will archive a copy of the authenticated document that was issued to the promoter. Given the high volume and complexity of the pre-processing and analyses of PET-MRI and EEG data, the outcome measures cannot be added to the eCRF and will be handled by the expert investigators.

### Data analyses

We will accept a significance level of 5% (*p* < 0.05) corrected for multiple comparisons when needed. To assess our primary endpoint criterion, i.e., performance changes on the SA task, outcomes at baseline and at the 2-week time point will be compared using two-way analysis of variance with “time” (baseline, 2 weeks post-stimulation) and “group” (anodal, cathodal, sham) as factors. Since two comparisons will be made (sham versus left-anodal and sham versus right-cathodal tDCS) Dunnett’s two-tailed *t* test will be used to handle multiple comparisons. In the case that the data do not meet the normal distribution assumption, the non-parametric Mann-Whitney test will be used to compare performance improvements between the sham versus left-anodal and between the sham versus right-cathodal groups.

To assess the time course of potential improvements and test if such differ between the treatment groups, linear mixed models will be used with “time” (the four time points), “group” (anodal, cathodal and sham) and group-by-time interactions as fixed effects. The Benjamini and Hochberg method will be used for controlling for false discovery rate.

To identify imaging bio-markers of stimulation-induced neuroplasticity, we will analyze cortical metabolism and resting-state functional connectivity. PET images will be used for cortical metabolism, to analyze tissue metabolic activity and regional glucose uptake in the brain. A voxel-based analysis, using the Statistical Parametric Mapping (SPM) software [66], will be implemented to highlight regional differences in metabolism between the images obtained at baseline and post-stimulation. The resting-state fMRI sequence will be explored to study the status of functional connectivity within the language/semantic networks and possible alterations within it between baseline and post-stimulation images. Quantification of functional connectivity will be based on integration measures in specific networks established from the known anatomy, on indices derived from the graph theory or information theory. Cortical regions of interest will be obtained automatically using SPM toolboxes. More specifically, the language/semantic network will include the middle and anterior portions of the lateral ATL, the inferior frontal gyrus, the dorsomedial and ventromedial prefrontal cortex and the inferior parietal lobe. To study the neurophysiological impact of tDCS on specific brain networks, resting-state EEG datasets obtained at baseline and 3 days after the end of the 10 tDCS sessions will be also analyzed. Data will be filtered (4–40 Hz) and power distribution and local synchrony calculated across frequency bands and compared. Functional connectivity maps across the electrodes will be estimated by calculating the phase-lockimg value between the eight EEG leads and have them compared across in pairs.

To identify biomarkers that could individually predict an efficient tDCS impact, 3D-T1 and DTI sequences will be explored and individual computational models of tDCS current will be produced. Structural 3D-T1 MRI data will be studied using surface-based cortical thickness analysis. An ROI will be defined in the ATL and cortical thickness values at baseline between a group of eventual “responders” (mean improvement of 15% in correct responses in the SA test) and “non-responders” to the stimulation will be compared using a general linear model. Diffusion MRI data will be studied using ROI analysis of DTI metrics. Fractional anisotropy (FA) and mean diffusivity (MD) maps will be calculated and the integrity of a set of anatomical white matter tracts will be assessed (FA and MD measures in each tract). The tracts analyzed will include bilaterally the inferior longitudinal fasciculus, the uncinate fasciculus, the superior longitudinal fasciculus, the inferior frontal-occipital fasciculus and different corpus callosum tracts connecting the left and right temporal lobes. This will allow a detailed anatomical analysis of white matter fiber tracts and compare their status between a possible group of responders and non-responders. The individual computational models of tDCS current magnitude will be used to identify which anatomical characteristics influence the amount of current reaching the target in the brain and if such measure can help predict the response to stimulation. Finally, the analyses of DTI data will also allow us to explore connectivity between the left and right ATL to improve the understanding of the semantic roles of each of these regions while contributing to the definition of anatomic-functional models of semantics.

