### Language/semantic tasks

A set of computer-based language/semantic tasks is used to assess the potential effectiveness of tDCS. These tasks are carried out by patients at four time points: pre-tDCS (baseline) and 3 days, 2 weeks and 4 months after the end of the 10-day tDCS regime. The five language/semantic tasks are the following:
Semantic association task (SA)Picture naming task (NAME)Reading task (READ)Letter and category fluency task (FLU)Category judgment task (CJ)

Two additional tasks evaluating tDCS impacts on other cognitive functions are also applied:
Executive function task (EXE)Recognition of famous faces - a subtest of the French *Batterie Imagerie-Perception* (BIP).

The tasks are computer-programmed using E-Prime software (E-Prime®, Psychology Software Tools, Sharpsburg, PA, USA). Participants are comfortably seated in front of a laptop computer screen (HP EliteBook 8770w, USA) and a response box that records responses. Performance accuracy, reaction times and voice records are automatically registered by the software. The sessions are carried out in the presence of an investigator immediately after familiarization/training blocks comprising five trials for each task.

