### PET-MRI neuroimaging and EEG recording

Neuroimaging data (PET, MRI) are collected before the tDCS sessions (baseline) and 2 weeks after the tDCS sessions. These acquisitions provide all the sequences underlying the following explorations: cortical metabolism, gray matter thickness measures, white matter fiber tracking and functional connectivity. The examination is performed on a hybrid PET-MRI scanner (Signa 3 T GE Healthcare, USA). The injection of FDG (Fluoro-Deoxy-Glucose 2-18F: MÉTATRACE®, half-life of 109,77 min, or GLUSCAN®, half-life of 110 min) is performed if the blood glucose checked prior to injection is ≤ 1.5 g/l. Participants lie in neurosensory rest in a quiet and unlit room for at least 30 min post-injection, prior to image acquisition.

The acquisition of brain images with PET is conducted in *list mode*. It begins 30–40 min after injection of the radiopharmaceutical FDG tracer and lasts for 20 min (3 × 5 min). Images are reconstructed and corrected for physical phenomena. They are expressed in standard uptake value (SUV). Magnetic resonance images are acquired simultaneously and include two anatomical sequences (3D-T1, 3D-FLAIR), a functional imaging sequence (resting state fMRI) and a diffusion tensor imaging (DTI) sequence.

Additionally, prior to and following stimulation, the tDCS device (Startsim, NEuroelectrics, Barcelona) automatically records brain activity through EEG scalp electrodes (sampling at 1500 Hz, low-pass high-pass filter 4–40 Hz). Resting-state EEG recordings are obtained from 10 to 20 EEG system locations F4, F3, C4, C3, P4, P3 and T8, T7.

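### The primary SA contrast uses only baseline and the 2-week visit, so 3-day and 4-month scores of a patient who misses 2 weeks are unused, although the planned four-visit model would use them

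*Protocol article*

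**What the plan says.** Under Sample size, the primary criterion is the 2-week change in the percentage of correct SA responses. Under Data analyses, the primary method is a group-by-time analysis of variance on two visits: "outcomes at baseline and at the 2-week time point will be compared using two-way analysis of variance with “time” (baseline, 2 weeks post-stimulation"). Each active arm is compared with sham by a two-tailed Dunnett test. If the data are not normal, "the non-parametric Mann-Whitney test will be used to compare performance improvements" between sham and each active arm.

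The SA task is also done at two other follow-up visits. Under Language/semantic tasks the schedule is "pre-tDCS (baseline) and 3 days, 2 weeks and 4 months after the end of the 10-day tDCS regime". The next paragraph of Data analyses plans a model that covers all of them, but for the time course only: "linear mixed models will be used with “time” (the four time points), “group” (anodal, cathodal and sham) and group-by-time interactions as fixed effects".

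Data management says that missing values are coded. The article gives no expected loss rate, no allowance for loss in the sample size, and no rule for a missing 2-week score.

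**The concern.** A group-by-time contrast on two visits is a comparison of mean changes. A patient without the second score has no change and cannot contribute, and the same holds for a rank test on improvements. Such a patient may still have a baseline, a 3-day and a 4-month score, all of which say something about the missing value.

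Two things are at stake. One is precision, in arms of only 20. The other is selection. If patients with a poor 3-day result are less likely to have a 2-week score, the 2-week completers look better than the arm as a whole. If that happens more in sham than in the active arms, the completer contrast is pulled toward no effect. A mixed model that includes the 3-day score corrects this when missingness depends only on observed scores. The protocol already plans that model but does not use it for the primary answer.

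**Working it through.** **Inputs from the article.** 20 patients per arm, expected difference in mean change 15 points, SD 16 (Sample size); two-tailed 5% level with Dunnett for two comparisons with sham (Data analyses).

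**Assumptions.** 5 to 20% of 2-week scores missing; correlations as given below. The article supplies neither.

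**Step 1: the stated power.** SE of a difference = 16 × √(2/n). At n = 20 this is 5.06, and 15/5.06 = 2.96. An unadjusted two-sided t test has 82.4% power at 20 per arm and 80.3% at 19, so the stated 80% with 20 is reproduced within two patients. With Dunnett (critical value about 2.27, 57 df) per-comparison power at 20 is about 75.5%, and 22 per arm are needed for 80%. That gap belongs to the sample size, not to this point. It does mean there is no spare margin for loss on a per-comparison basis.

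**Step 2: two-visit analysis after equal loss in all arms.** Noncentral t with noncentrality 15/(16√(2/n)) and the Dunnett critical value at each n. Either-arm power assumes that both active arms have the 15-point effect.

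| Analysed per arm | SE | Per-comparison power | Either-arm power |
|---|---|---|---|
| 20 | 5.06 | 75.5% | 88.1% |
| 19 | 5.19 | 73.2% | 86.3% |
| 18 | 5.33 | 70.4% | 84.3% |
| 17 | 5.49 | 67.5% | 82.0% |
| 16 | 5.66 | 64.5% | 79.5% |

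**Step 3: what the four-visit model recovers.** Assume compound symmetry with correlation ρ from 0.5 to 0.8, score SD = 16/√(2(1 − ρ)) so that the change has SD 16, and 3-day and 4-month scores kept. With k of 20 patients per arm lacking the 2-week score and V the 4 × 4 covariance, the arm's information is A = (20 − k)V⁻¹ + k(V without 2 weeks)⁻¹, with zeros in the 2-week row and column of the second term. The variance of the contrast is 2c′A⁻¹c with c = (−1, 0, 1, 0). Power is Φ(15/SE − 2.265), a normal approximation with known covariance, so the two-visit figures differ by up to about half a point from Step 2.

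| 2-week scores missing | Two-visit completers | Four-visit model | Gain in points |
|---|---|---|---|
| 5% (k = 1) | 73.4% | 74.2–74.3% | 0.8–0.9 |
| 10% (k = 2) | 70.8% | 72.5–72.6% | 1.7–1.8 |
| 15% (k = 3) | 68.0% | 70.6–70.8% | 2.6–2.8 |
| 20% (k = 4) | 65.0% | 68.6–68.9% | 3.6–3.9 |

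**Step 4: bias.** Let the chance of a missing 2-week score rise as the 3-day change falls, with logistic slope 1 per SD, and let the 3-day and 2-week changes correlate at r = 0.5 to 0.7. The completers' mean 2-week change is then too high by 16 × r × (mean standardised 3-day change among completers).

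- 20% missing: completer mean 0.173 SD, so 16 × 0.5 × 0.173 = 1.4 to 16 × 0.7 × 0.173 = 1.9 points.
- 10% missing: completer mean 0.091 SD, so 0.7 to 1.0 points.
- 20% in sham and 10% in active: 16 × r × (0.091 − 0.173) = −0.7 to −0.9 points, toward no effect.
- 15% in every arm: the two terms cancel and the bias is zero.
- 25% in sham and 5% in active: −1.3 to −1.9 points.

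The 20%/10% split is what one common rule implies. If 20% of sham patients are lost and the active arms sit 15 points (15/16 SD) higher at 3 days, the same rule loses about 10% of active patients. Against the SE of 5.06, 0.7 to 0.9 points is 0.14 to 0.18 SE. Adjusting for the observed 3-day score brings the error to about zero.

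**The case against.** The strongest reply is that the two-visit comparison estimates the declared endpoint directly and that the four-visit model is planned as well, so the 2-week contrasts from all scores will exist either way. Much of this stands. The choice is defensible, and what is at issue is which analysis carries the primary claim.

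Some stronger readings are tempting, and the article does not support them.

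- A reader might infer that patients without a 2-week score will be excluded as a rule. The article does not say so. An imputation rule could exist in a full protocol or analysis plan that is not shown, though nothing in the article points to one. The point concerns the two methods that are named.
- A reader might infer that the 2-week visit is the easiest to miss, because "Neuroimaging data (PET, MRI) are collected before the tDCS sessions (baseline) and 2 weeks after the tDCS sessions". Nothing makes the SA task conditional on imaging, and patients with imaging contraindications are not included. The one patient reported as unable to have the scans was at screening. Trial status mentions no missed visit.
- A reader might say that the ANOVA is unbiased only if missingness is unrelated to outcome. For the between-arm difference that is too strong: equal loss under the same mechanism cancels.
- The 25%/5% split does not follow from one common missingness rule and should not be used to size the problem.
- Per-comparison power alone looks pessimistic. Sample size counts the trial as positive if either active arm beats sham, and that power is 88% at 20 and 84% at 18 per arm.

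It is also fair to say that a normal-theory mixed model needs an answer for non-normal data, which the protocol now gives through the Mann-Whitney test.

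**Conclusion.** The point holds as a modest improvement that costs little. As written, neither the ANOVA contrast nor the Mann-Whitney fallback can use a patient who lacks the 2-week SA score, while a model already in the plan can. For 5 to 20% missing 2-week scores the gain is about 1 to 4 points of per-comparison power. If loss follows the 3-day change at 20% in sham and 10% in active, the model removes a bias of about 0.7 to 0.9 points toward no effect. With no treatment effect and one rule across arms there is no bias, so this mechanism does not produce false positives.

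All of this depends on assumed loss rates, correlations of 0.5 to 0.8, equal loss for the power figures, and missing at random for the bias correction. The article gives no figure for any of them. The main value lies in keeping more randomised patients in the primary answer.

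**What to change.** In Data analyses, take the primary result from the planned four-visit mixed model. Fit time as categorical and include every randomised patient with a baseline and at least one follow-up SA score. Report the 2-week sham-versus-anodal and sham-versus-cathodal contrasts in change from baseline, with the Dunnett adjustment. Keep the two-visit ANOVA and the Mann-Whitney test on improvements as sensitivity analyses; the latter covers non-normal data.

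The cost is a few sentences, with no new visits, data or patients. At publication 13 of 60 patients had been randomised, so the change could have been fixed before unblinding. The downside is reliance on missing at random and on the chosen covariance structure. A patient with no follow-up score is still not helped.
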